### Outcomes

The primary outcome is pilonidal disease recurrence at 1 year, defined as development of a new pilonidal abscess, folliculitis, or draining sinus after treatment, which would require antibiotic treatment, additional surgical incision and drainage, or excision. Secondary outcomes include each of the following at 1 year: disability days of the patient, disability days of the caregiver, HRQOL, healthcare satisfaction, disease-related attitudes and perceived stigma, pilonidal disease-related complications, pilonidal disease-related procedures, surgical excision, postoperative complications, and compliance with recommended treatment.

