### Statistical considerations

#### Sample size and power

The sample size needed to assess the primary outcome of the proportion of patients with recurrent pilonidal disease at 1 year is based on (1) previous published studies and institutional data on pilonidal disease recurrence rates and (2) the efficacy of laser hair depilation treatment to reduce pilonidal disease recurrence in previous studies and our institutional pilot study. In this RCT, the recurrence rate within 1 year is expected to be a minimum of 12% in the control group and a maximum of 2% in the laser group. Based on these estimated recurrence rates, under a group sequential design with one interim and one final analysis, an overall type I error rate (two-sided) of 5%, and power of 80%, the sample size required for this trial is 122 patients in each treatment group. Assuming a 10% drop-out rate over the course of the 1 year follow-up, we will plan to enroll 136 patients in each group for a total of 272 patients.

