#### Planned interim analysis

An interim analysis is planned when one quarter of the planned total patients (34 patients in each group) have completed their 1 year follow-up, and a final analysis will be performed when all patients have completed 1 year of follow-up. These two analyses have been unequally spaced in order to ensure that the interim analysis is performed before study enrollment is complete.

Throughout the trial, the rate of pilonidal disease recurrence at 6 months and 1 year and the tolerance of laser treatments are monitored for safety. Tolerance to the laser treatments is monitored by examining for study-related serious adverse events (SAEs), which include severe pain (defined as a maximum pain score of 8 or above during or within 24 h of treatment) or second degree burns. The rates of SAEs are calculated after every group of 10 patients has completed the course of treatment. The percentage of patients with either a second degree burn or a maximum pain score of 8 or above during or after treatment is estimated. If the lower 95% confidence limit of this proportion exceeds 10%, the trial will be stopped. The 10% level was chosen based on input from patients involved in our feasibility and tolerability pilot in which they expressed that even if they had experienced acute pain or a minor burn, they would likely continue receiving therapy, as these both are self-limited events with minimal long-term morbidity. These rates are regularly reported to the Data and Safety Monitoring Committee (DSMC).

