Analyses of secondary outcomes will also follow an ITT approach. Categorical secondary outcomes (e.g., complications) will be assessed using estimated proportions and confidence intervals and compared between groups using Fisher exact tests or Pearson chi-square tests as appropriate, similar to the primary outcome. Continuous secondary outcomes (e.g., HRQOL) will be assessed using medians and interquartile ranges and compared between groups using Mann-Whitney *U* tests. These are hypothesis-driven analyses, with the laser group expected to have less disability for both the patient and caregiver, higher HRQOL scores, higher healthcare satisfaction scores, more favorable disease-related attitudes and perceived stigma, lower rates of pilonidal disease-related complications, lower rates of incision and drainage, lower rates of surgical excision, lower rates of postoperative complications, and higher compliance with treatment. We will give specific consideration to the potential for varying treatment effects across groups defined by the four patient characteristics described in the preceding paragraph. In further exploratory analyses, we will examine the complete longitudinal trajectory of both patient- and guardian-reported HRQOL, satisfaction with healthcare, and disease-related attitudes and perceived stigma through the use of linear mixed effects models [26]. In addition, both primary and secondary endpoints will be examined, though not formally statistically compared, across various subgroups defined by patient socioeconomic status (SES) and demographic characteristics, including race, ethnicity, insurance status, household annual income, and number of household residents. These subgroup analyses will be exploratory rather than confirmatory.

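### Patient and caregiver disability days get a median, an IQR and a p-value but no effect estimate; if recurrence drives the missed days, both arms are likely to read 0 (0–0)

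*Protocol article*

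**What the plan says.** The Outcomes section lists "disability days of the patient, disability days of the caregiver" as separate secondary outcomes at 1 year. The Analytic plan expects both to be lower with laser.

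For secondary outcomes the Analytic plan gives two rules. Categorical outcomes (complications are the example) get proportions with confidence intervals and a Fisher or chi-square test. Continuous outcomes (HRQOL is the example) "will be assessed using medians and interquartile ranges and compared between groups using Mann-Whitney" U tests. Disability days are named under neither rule. As a count of days they fit the second. The linear mixed models cover HRQOL, satisfaction, attitudes and stigma, but not disability days.

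Sample size and power expects 1-year recurrence of "a minimum of 12% in the control group and a maximum of 2% in the laser group". Table 2 lists days missed from work or school and from normal activities as items of their own, separate from recurrence.

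**The concern.** A median and IQR describe the middle half of a distribution. When more than three quarters of an arm has the value zero, they read 0 (0–0) whatever happens to the rest. Disability days in patients enrolled after their acute episode has settled could well look like this, because most are expected to have no recurrence during the year.

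The plan offers nothing else for these outcomes: no mean, no difference, no confidence interval. The trial could then report a significant Mann-Whitney result beside two identical summaries and leave the reader unable to tell how many days of school, work or activity laser saves. The Background names disease-related disability among the outcomes important to patients, so this answer matters to the trial's audience.

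**Working it through.** **Inputs from the article.** Recurrence 12% (a floor) and 2% (a ceiling); 122 per arm analysed, 136 enrolled; five laser visits. The 122 reproduces: a continuity-corrected two-proportion calculation gives 121, times an O'Brien-Fleming inflation of 1.0002 at one quarter of the information = 121.02, rounded up to 122; 122 / 0.90 = 135.6, so 136. The article gives no figure for disability days.

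**Assumptions, not in the article.** Days per recurrence, d: mean 6.5 (gamma with shape 1.5 and scale 4, rounded up), or mean 5 (1 + Poisson(4)) as an alternative.

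**Step 1: recurrence as the only source of days.** The zero shares are 1 − 0.12 = 88% and 1 − 0.02 = 98%. The upper quartile leaves 0 only if more than 25% of an arm has a missed day, and the median only if more than 50% has.

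- Control, exact binomial at 12%: P(share > 25%) = 0.00004 at n = 122 and 0.00001 at n = 136.
- Laser, at 2%: negligible.

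So both arms read 0 (0–0), whatever d is.

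**Step 2: what that hides.** Mean days are 0.12d and 0.02d, a difference of 0.10d.

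| d (assumed) | Control | Laser | Difference |
|---|---|---|---|
| 5 | 0.60 | 0.10 | 0.50 |
| 6.5 | 0.78 | 0.13 | 0.65 |

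In 4,000 simulated trials with d = 5, both medians and both upper quartiles were 0 in every run, and Mann-Whitney was significant at 5% in about 90%.

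**Step 3: other sources of days.** Let a share q of patients without recurrence also miss at least one day. With recurrence rate r, the upper quartile leaves 0 when q > 1 − 0.75/(1 − r), and the median when q > 1 − 0.50/(1 − r).

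| Arm | q for upper quartile | q for median |
|---|---|---|
| Control (r = 0.12) | 14.8% | 43% |
| Laser (r = 0.02) | 23.5% | 49% |

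If each of the five laser visits costs a day with independent probability v, the laser share with any day is 1 − 0.98(1 − v)^5: 24% at v = 5%, 42% at 10%, 68% at 20%. The laser upper quartile leaves 0 at about v = 5.2% and the median at about 12.6%.

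**Step 4: can the medians rank the arms the wrong way?** Suppose a share s of laser patients loses one day to visits and control patients lose none.

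- Laser median above 0: s > 0.49.
- Laser mean still lower: 0.02d + s < 0.12d, so s < 0.10d.

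At d = 6.5 the window is 0.49 < s < 0.65. At s = 0.58 the laser mean is 0.13 + 0.58 = 0.71 against 0.78, yet the laser median exceeded the control median in 97% to 98% of simulated trials. At d = 5 the window shrinks to 0.49–0.50. Reversal is possible, but it needs particular values.

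**The case against.** **The share of zeros is not in the document.** A reader might infer that the 12% and 2% force the summary to 0 (0–0). They do not. They are recurrence rates; nothing ties missed days to recurrence, and the follow-up sections survey healthcare-associated disability at every contact. Clinic visits, treatment pain or milder symptoms could add days. Step 3 shows that modest additions move the upper quartiles. This stands, and it makes the point conditional.

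**12% is a floor.** The Discussion cites recurrence of up to 30% after less invasive measures. If 30% of controls had a missed day, their upper quartile would exceed 0 with probability 89% at n = 122. This also stands, but the control median would remain 0 (probability of exceeding 0 about 0.000001), and there would still be no effect estimate.

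**Visit days need not mislead.** A reader might infer that any visit burden makes the medians point the wrong way. At half a day per visit, laser patients average 5 × 0.5 + 0.13 = 2.63 days against 0.78, so a higher laser median ranks the arms correctly. Reversal occurs only in a range such as that in step 4.

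**The test is sound.** Mann-Whitney remains valid with many ties and had about 90% power in the simulated case. A reader should not infer an inferential error; the weakness lies in the summary.

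**Effects are estimated elsewhere.** The Analytic plan promises treatment effects by factor level for secondary outcomes. These are subgroup estimates, with no model or measure named for day counts, so they do not fill the gap.

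**It may be left to an unseen SAP.** Disability days are not assigned by name, and a fuller plan may already add an estimate. But the article states a method for the whole continuous class, so the point concerns a stated choice.

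**Conclusion.** The point holds in conditional form. The stated rule for continuous secondary outcomes gives no between-group effect measure, and it is poorly suited to day counts with many zeros. If recurrence is the main source of missed days, both arms will almost certainly read 0 (0–0), while the means differ by about 0.5 to 0.65 day per patient for an assumed 5 to 6.5 days per recurrence. If visits or other causes contribute, the quartiles may become informative or, in a limited range, the medians may contradict total days lost.

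This rests on three assumptions: that disability days fall under the continuous rule, that the planning rates are roughly right, and that the days per recurrence are as assumed. The 0 (0–0) result under recurrence alone does not depend on the last. No planned test is wrong and the primary analysis is unaffected. The change is worth making because two outcomes important to patients would otherwise lack an interpretable size of effect.

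**What to change.** For patient and caregiver disability days, keep Mann-Whitney as planned and add:

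- mean days per patient in each arm;
- the difference in means with a bootstrap 95% confidence interval;
- the proportion with any day lost in each arm, with a confidence interval (the Wilson method already chosen for the primary outcome would serve).

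State in the Analytic plan that these apply to disability days by name, which also settles which rule governs them. Show days lost to laser visits separately only if the survey already records the reason for a missed day. Table 2 is a sample list and shows no such item, so this part may not be possible with the data as collected.

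The cost is a little more analysis on data already being collected. The mean is sensitive to a few long absences, which is why the proportion with any day and the rank test should stand beside it.

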### Safety monitoring

The attending surgeons and staff in the surgical clinic are managing the clinical care of the participants. Vital signs, physical exam, and pain scores are assessed per nursing protocol and surgical service standards. An attending surgeon assesses each patient before and after each treatment. A research team call schedule is maintained, with a member of the study team available by pager 24 h per day. Any suspected adverse event (AE) identified by this person is discussed with the study principal investigator (PI). A DSMC has been formed and will meet every 6 months throughout the period during which patients are being recruited and through their first year of follow-up. The DSMC will review data provided by the primary study statistician and other study staff involved in data management and analysis. The study PI will be made aware of all AEs as they occur, and a quarterly review of all AEs that occur in the trial will be performed by the study team. All unexpected non-serious AEs and SAEs relating to participation in the study will be reported verbally and in writing to the study PI and the NCH Institutional Review Board (IRB). The verbal report will occur within 48 h of the occurrence. The written report of a SAE (e.g., death or a life-threatening AE) will be reported within 7 days.

### Study retention

Study retention is promoted by providing Mastercard® ClinCard incentives for completing follow-up assessments, by using regularly scheduled short interval contact with the participants throughout the 1-year duration of the study, and by providing multiple methods for follow-up including phone, email, and text.

## Discussion

The results of this study will be important, because the incidence of pilonidal disease in the adolescent population is high, and few effective treatments exist presently. Recurrence rates after less invasive measures, including antibiotics and/or incision and drainage, have been reported to be as high as 30% [27]. Recurrence rates after surgical excision, considered to be the gold standard treatment for recurrent pilonidal disease, are also high [27, 28]. In addition, patient morbidity after surgical excision is considerable, with a significant percentage of patients suffering from severe wound complications postoperatively [29]. Thus, treatments are clearly needed to prevent the significant morbidity caused by not only the disease, but also the surgical treatments currently available. The success of laser hair depilation to reduce pilonidal disease recurrence may prevent many patients from developing chronic infections and wounds, thereby reducing the number of patients subjected to the significant morbidity of this disease. Positive results from this study may transform the treatment paradigm of pilonidal disease—from one in which patients, families, and physicians anticipate recurrences, to one in which a less invasive office-based therapy may eradicate the disease entirely.

Multiple groups have acknowledged the efficacy of laser hair depilation to prevent recurrence of pilonidal disease [11, 19,18, 30–32, 33]. However, these groups believe that additional well-controlled prospective studies are critical for establishing its effectiveness prior to recommending it to all patients. This study aims to determine the effectiveness of laser hair depilation to decrease the recurrence of pilonidal disease in adolescents and young adults. To maximize the generalizability of our results, all patients with mild to severe disease are being enrolled. Results from this study should be able to be widely disseminated and applied to the treatment of pilonidal disease in adolescent and adult patients.

### Trial status

This RCT began enrolling patients in September of 2017. Active enrollment is open and over 50 patients have been enrolled as of 10/25/2018.

## Abbreviations

BMI: Body mass index
CATIS: Child Attitude Toward Illness Scale
DSMC: Data and Safety Monitoring Committee
HRQOL: Health-Related Quality of Life
ITT: Intention to treat
NCH: Nationwide Children’s Hospital
NRS: Numeric rating scale
OSU: Ohio State University
PedsQL: Pediatric Quality of Life
SAE: Serious adverse event
